#### 3. Process evaluation

Our process evaluation is informed by realist approaches to intervention theory [47] which stress the importance of context in understanding mechanisms of change; what “works” in one time and place may be ineffective, or even harmful, elsewhere. This is reflected in our working process evaluation framework, which guides exploration of key process evaluation domains as detailed in Table 3.

**Table 3 Tab3:** Working process evaluation framework

Research domain		Research questions
Implementation	Fidelity & quality	How did implementation of SIPP intervention vary from what was planned, i.e. (a) recruitment of PWUC at all sites, (b) training and protocols delivered, (c) provision of SIPP kits, (d) active engagement of peer networks, (e) SIPP harm reduction materials developed and used
*What is implemented and how?*		What were the barriers and facilitators to implementation fidelity?
		What adaptations were made?
	Coverage (reach & dose)	How many: (a) PWUC were approached across all sites, (b) PWUC took up SIPP kits and/or peer-led harm reduction training (c) PWUC were referred or linked to specialist drug services, and (d) local law enforcement and/or government authorities maintained support
		What were the barriers and facilitators to each of the above?
Mechanism of impact	Acceptability & feasibility	Which components of the intervention were best accepted and adopted by PWUC, peer-network members, providers, and health system/policy stakeholders? What were the experiences and perceptions of PWUC who were actively, somewhat or not at all engaged with harm reduction and SIPP uptake? What were the challenges and barriers faced?
*How does intervention lead to change?*	Interactions & consequences	How did various components of the intervention interact (i.e. SIPP kit provision, peer-network harm reduction outreach, uptake of specialist drug services)?
		Were there any unanticipated pathways or consequences?
Context	Proximal and distal	What social, cultural, political, and logistical factors impede or facilitate (or were affected by) how the intervention was implemented across the different sites
*How context affects implementation & outcomes?”*		What were contextual reasons for adaptations to the intervention and its delivery?

##### Sample

We will interview 36–45 people who use crack across the intervention sites (12–15 per site), with interviews spanning the pre-post-survey and intervention periods. We will purposively sample for variation in gender, ethnicity and age. A smaller number of people (6–9), sampled for duration of crack use (5 + years), will be recruited at the control sites (2–3 per site) to obtain an understanding of local crack use practices and market dynamics. Peers and providers involved in delivering the SIPP survey and intervention will facilitate recruitment. Clients meeting our purposive sampling criteria will be informed of the qualitative arm of the study and provided with a participant information sheet. If interested, they or the peer/provider can facilitate research team contact. We will also interview 15–18 service providers and peer researchers involved in survey and intervention delivery across the sites and select stakeholders (police, commissioners) purposively sampled to reflect variation in relevant occupational roles (*n* = 5–8). Stakeholders will be recruited through professional networks, and peers/providers through the engagement of the research team at each site. Total qualitative interviews 62–80. Flexibility in recruitment numbers allow for theoretical sampling. This is a grounded theory technique whereby early analysis of purposively sampled participant data allows for additional targeted sampling to address analytic gaps, puzzles or leads [48].

##### Data generation

We will employ qualitative methods (ethnographic observations, in-depth interviews) to: (i) explore the local social contexts and relations of drug use, risk practices, health concerns and service engagement/need over time (from pre to post-intervention), (ii) document and assess delivery of each component of the SIPP intervention, (iii) explore client and provider expectations, experiences, perceptions and interactions with the SIPP intervention; (iv) examine local contextual factors that may influence the effectiveness of the intervention as designed. Ethnographic observations will be recorded in anonymised field notes by each research team member, detailing each study site visit from pre through to post-intervention. Together, these will elaborate the local contextual features of each site, with attention to the social relations, resources and environments informing practices of drug use, risk and care, as well as the internal/external relations and resources informing drug service and policing practice and policy. Interviews will be informed by topic guides oriented to exploring the domains noted above (i to iv). Finally, monitoring data collected by service providers alongside SIPP kit delivery will enable assessment of intervention coverage and reach (e.g. how many SIPP kits were distributed and to whom). Monitoring data categories comprise: place of engagement; numbers of pipes received; reason for new SIPP kit; component of kit received (whole kit, mouthpiece, filter, push stick); gender; ethnicity; engagement with service; reason for engagement; minimal identifiers (date of birth, initials).

##### Analysis

Interviews will be recorded and transcribed verbatim. Observation fieldnotes will be generated throughout and integrated alongside transcripts in analyses. Qualitative data will be managed in NVivo Software. We will conduct a thematic analysis comprising six stages: (i) data familiarisation; (ii) first-level open coding, (ii) coding framework development; (iii) second level inductive coding; (iv) category mapping; (v) thematisation; and (vi) write up. This process is a modification of Braun and Clarke’s [49] guidelines for thematic analysis, also incorporating grounded theory principles such as early analysis alongside data generation, process-orientated inductive coding and theoretical sampling [48].

We will triangulate analysis [50] with attention to: (a) multiple forms of qualitative data (interviews, observations); (b) multiple participant perspectives (service providers, stakeholders, PWUC from diverse communities, treatment engaged/disengaged); (c) multiple intervention sites; and (d) multiple time points (pre/during/post-intervention). The primary focus of triangulation will be to identify congruence and divergence, as well as to maximise the confidence with which judgements are made regarding potential relative intervention effects. Where possible, quantitative and qualitative analyses will build upon one another, qualitative to explore baseline survey data findings and to inform the impact evaluation – by providing insight into local secular changes at intervention sites, not captured by comparison site data. We will hold data analysis workshops with peer network and advisory board members, to "sense check" our interpretations, co-produce visual category mapping and discuss community feedback mechanisms, including through presentations and resource development.

To measure coverage including reach and dose of SIPP we will analyse monitoring data collected alongside the SIPP Kit delivery (see data generation above). Firstly, minimum identifiers will be used to link those that received SIPP with those that took a baseline and follow-up survey to assess what proportion of the population engaged with SIPP. Secondly, together with information on intervention activities (e.g. number of SIPP kits distributed), monitoring data will be analysed descriptively to assess the fidelity of the intervention (the extent to which it is delivering what it set out to do); intensity in which SIPP kits are used and by which population (age, gender, ethnicity); and reach (what proportion of the population are engaging in SIPP at each site). This will include assessing the lifespan of a SIPP kit, the number of first-time recipient's vs re-occurring recipients and trends in the number of SIPP kits being distributed during the intervention.

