### Study partners and sites

The SIPP study would not be possible without the support of local police forces, specialist drug service providers, community members and charity organisations working to support peer advocacy and involvement. Prohibition of crack pipe provision necessitated contact with local Chief Constables and Police and Crime Commissioners prior to study site selection. Our intervention sites in Bristol, Nottingham, and Mansfield, are under the jurisdiction of the Avon & Somerset Police and the Nottinghamshire Police, respectively. Both have provided written approval for SIPP kit distribution through our specialist drug service providers and peer-network partners for the six-month duration of the intervention.

Non-equivalent control sites have been selected for intervention site comparability, with attention to local geography, demographics and the number of people using specialist services for drug use type recorded as using crack cocaine. Geographical distance between control and intervention sites decreases contamination risk. The control sites are: Birmingham (for Bristol, conurbations); Coventry (for Nottingham, mid-sized cities); Leamington Spa and Nuneaton in Warwickshire (for Mansfield, Nottinghamshire, peri-rural/rural sites adjoining Coventry and Nottingham, respectively). Each intervention and control site has a primary partner who is specialist provider of services for people who use drugs, with additional peer network and outreach distribution supported by Coact (Bristol), The Hepatitis C Trust (Birmingham) and POW sex worker support service and outreach (Nottingham). See Table 2, below.

**Table 2 Tab2:** Intervention and non-equivalent control sites

Service type	Intervention site	Non-equivalent control site
Specialist drug service	Nottingham Health Shop/Well-being Hub	Change Grow Live—Coventry
Sex worker support service	POW Nottingham	
Specialist drug service	Bristol Drugs Project	Change Grow Live—Birmingham west
Peer network	Bristol COACT peer activist group	Hepatitis C Trust peer outreach—Birmingham
Specialist drug service	Change Grow Live –Nottinghamshire	Change Grow Live—Warwickshire

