### Study population

Our study population for the evaluation are people who use crack cocaine, defined as people who self-report smoking or injecting crack in the past 28 days. To participate they must be aged 18 years or over and have the capacity to consent. Excluded are those aged under 18 years; currently incarcerated; lacking capacity for informed consent; or with no history of crack use. We include people who inject crack as a SIPP target population, given the potential for inhalation equipment provision to support transitions from injection and reduce injection frequency.

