### Study components

#### 1. Peer capacity building and co-production

Community mobilisation and capacity building are central to the SIPP project design. We adopt a multi-pronged recruitment approach, working with community-based specialist services for people who use drugs but also peer activists and networks who are experienced in delivering harm reduction interventions to their communities. Through a dynamic process of peer researcher development and community mobilisation we will capacitate and evaluate peer-led provision of the SIPP intervention alongside provision through more traditional harm reduction services. Peers (i.e. people with past and/or present experience of crack use) in three sites (Bristol, Nottingham and Birmingham) will receive training in research methods, including those specific to SIPP, and be supported by the team to deliver each study component as appropriate to their location (intervention/control). At each site, 3–5 peers will generate pre- and post-survey data with a focus on recruiting people not accessing drug treatment services, women, and ethnic minorities. During the six-month intervention period peers in the intervention sites will distribute pipes and harm reduction advice, with a focus on reaching the underserved communities recruited during survey generation. All peer researchers will be remunerated for their time and expenses, including for training participation.

People who use crack have privileged access to the communities in which they live. Our peer-network team members provide unprecedented access to people who use crack who are not in touch with services. Peers are instrumental in transferring crack risk reduction knowledge [38] and providing support in the context of drug use, homelessness and exclusion [39, 41]. This project will add value by seeking to understand the barriers and facilitators to working with peer networks as research partners to inform future community-participatory research with marginalised populations. In addition, we will explore if the mode of SIPP delivery (peer network vs. drug treatment service) influences SIPP acceptability and reduction in risk practices. This knowledge has transferable value to inform scale up of other harm reduction and public health interventions for marginalised populations (NSP, vaccine rollout, etc.).

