##### Data collection

Two surveys will be conducted six months apart to allow for the intervention phase. For both the pre- and post-survey, a structured questionnaire will be administered by staff at specialist drug services and peer researchers, trained in data collection methods, informed consent procedures and all aspects of the study protocol. Service providers and peers will approach potential participants and current clients, describe the study and discuss contents of the information sheet and consent form. Participants who consent will complete a structured questionnaire in English on a Lenovo tablet device with the ODK collect app either self-completed or administered by a service provider or peer. The questionnaire takes approximately 30 min to complete and contains the follow sections: demographics (including age, gender identity, sexual orientation, ethnicity, and source(s) of income); drug use practices (including drugs taken, routes of administration, and equipment sharing/reuse); indicators of social exclusion (including housing status and healthcare access); policing (including recent arrest and history of incarceration); primary and secondary outcomes (see below). Our questionnaire has been developed with input from peers and service providers and incorporates measures used in comparable surveys with people who use crack in Canada and UK [2, 18, 27, 28, 30, 42] as well as drawing on a questionnaire piloted by peers in 2020 for SIPP study conceptualisation. We will not actively follow-up participants, but we will collect minimal identifiers (date of birth, initials) needed to link people over time to allow assessment of primary and secondary outcomes and new presentations at specialist drug services. The same questionnaire will be used to collect post-intervention survey data.

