##### Recruitment

We will recruit up to 740 people who use crack through participating specialist drug services at the intervention (*n* = 400) and control sites (*n* = 200) and via peer networks (*n* = 140). Peer network recruitment will happen at both intervention (*n* = 100) and control sites (*n* = 40).

We will recruit using both randomised and targeted sampling. We will attempt to recruit a randomised sample from specialist drug services, to reduce selection bias, but will be pragmatic considering difficulties in recruiting this marginalised population. The LSHTM team will work with specialist drug services to generate a randomised anonymised sample of clients who are eligible to participate in the study. The specialist drug services will start recruitment from this list contacting potential clients in line with standard service engagement practice and where appropriate invite people in to participate in the research. Should we fail to meet recruitment targets at week eight, recruitment will be opened to all eligible clients, irrespective of the list, including those attending for appointments, opportunistic walk-ins and referrals from friends. In addition, we will employ targeted sampling methods to recruit 140 participants representing diverse crack user sub-populations via peer networks to widen the evidence base on health needs and service access among people who use crack not currently engaging with services. Both pre- and post-surveys recruitment will be conducted over the course of 10 weeks with an additional 4-week extension if necessary.

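### Linking kit recipients to survey takers measures coverage among survey participants, but the plan reads the result as a proportion of the population

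*Protocol article*

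**What the plan says.** The Analysis section of the process evaluation (Protocol article) sets out two steps. In the first, minimum identifiers serve this purpose: "link those that received SIPP with those that took a baseline and follow-up survey to assess what proportion of the population engaged with SIPP". In the second, monitoring data and activity counts are used to describe fidelity, intensity and "reach (what proportion of the population are engaging in SIPP at each site"). No denominator is named for the second step.

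The Study population section defines whom the evaluation is about: "Our study population for the evaluation are people who use crack cocaine, defined as people who self-report smoking or injecting crack in the past 28" (a window counted in days). Contact with a service is not a condition.

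Other sections show who reaches these people:

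- **Kits.** Police approval is for "SIPP kit distribution through our specialist drug service providers and peer-network partners" (Study partners and sites).
- **Surveys.** "Service providers and peers will approach potential participants and current clients" (Data collection).
- **Peer targeting.** Over the six months of kit supply, "peers in the intervention sites will distribute pipes and harm reduction advice, with a focus on reaching the underserved communities recruited during survey generation" (Peer capacity building and co-production).
- **Sample mix.** Intervention sites plan 400 participants through services and 100 through peer networks (Recruitment).
- **Sampling at services.** Services start from a randomised list of eligible clients. If targets are missed by the eighth week, the rule changes: "recruitment will be opened to all eligible clients, irrespective of the list, including those attending for appointments, opportunistic walk-ins and referrals from friends" (Recruitment).
- **Follow-up.** Participants are not actively followed up between surveys (Data collection).

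**The concern.** A proportion of the population needs a denominator that represents the population. Here it is a set of people found through the channels whose output is being measured. Someone unknown to these services and peers can hardly enter the denominator, and is also the least likely to receive a kit. Leaving such people out raises the figure.

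The dependence is stronger for the second survey. With no active follow-up, taking it largely requires renewed contact with the services or peers that distribute kits. The study also expects kits to draw people into services, since increased presentation is a secondary outcome, so kit receipt may itself lead to being surveyed.

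Reach is part of objective 3 (Table 1) and a coverage domain of the process framework (Table 3). It would inform scale-up. If coverage of contacted people is reported as coverage of all people who use crack, planners could believe that the hidden group, whose needs motivate the study, had been reached.

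**Working it through.** The plan states no reach or uptake figure, so there is none to reproduce. All uptake and participation values below are assumptions.

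**1. Route mix**

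Inputs from the document:
- The service share of the intervention sample is 400/500 = 80%, and the peer share is 100/500 = 20% (Recruitment).
- Nationally, 29% of people who use crack use neither heroin nor opioid substitution therapy and are less likely to be in touch with services (Background). The complement, 71%, is a rough proxy for the share in contact.

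Let u_s and u_o be kit coverage in and out of service contact, and f the in-contact share of the local population. Peer recruits are treated as typical of people outside services.

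- Survey figure = 0.8·u_s + 0.2·u_o
- Population figure = f·u_s + (1 − f)·u_o

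With u_s = 60% and u_o = 20%, the survey figure is 0.8 × 0.60 + 0.2 × 0.20 = 52%.

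| f | Population figure | Gap (points) |
|---|---|---|
| 80% | 0.48 + 0.04 = 52% | 0 |
| 71% | 0.426 + 0.058 = 48.4% | 3.6 |
| 60% | 0.36 + 0.08 = 44% | 8 |
| 50% | 0.30 + 0.10 = 40% | 12 |
| 30% | 0.18 + 0.14 = 32% | 20 |

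With u_s held at 60%, u_o from 10% to 40% and f from 30% to 71%, the survey figure is 50–56% and the population figure 25–54%. The ratio runs from 1.03 to 2.0. If u_o = u_s there is no gap. If f exceeded 80%, the sign would reverse in this simple model. Peers aim kits at the communities they surveyed, so their recruits probably have higher coverage than other people outside services. That would widen the gap.

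**2. If the denominator is people with both surveys (one reading)**

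Let c be uptake among baseline participants, and a and b the second-survey participation of recipients and non-recipients.

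Coverage among those with both surveys = c·a / [c·a + (1 − c)·b]

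With a = 75%:

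| c | b = 75% | b = 50% | b = 40% |
|---|---|---|---|
| 50% | 50% | 0.375/0.625 = 60% | 0.375/0.575 = 65% |
| 30% | 30% | 0.225/0.575 = 39% | 0.225/0.505 = 45% |

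The gap is zero when participation is equal, and 9 to 15 points in the other cells.

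**3. Missed matches**

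Linkage uses initials and date of birth. A recipient who fails to match is counted as a non-recipient, which lowers the figure. If 75% of true recipients matched, the ratios in step 1 become 0.75 × 1.03 ≈ 0.8 to 0.75 × 2.0 = 1.5. This 75% is an assumption. The document's own 75% (Sample size) concerns linkage between the two surveys.

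**The case against.** Several parts of the opposing case stand.

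- **Both-surveys denominator.** A reader might infer that only people with both surveys count. The wording can equally mean respondents to either survey. Outcome measures describes linking survey data to monitoring data without that restriction, and the per-protocol analysis states the restriction openly where it is meant. Step 2 of the working therefore applies to one reading only.
- **Site-level reach.** A reader might infer that reach at each site is also obtained by this linkage. The text places it in the second step and names no denominator. In a condensed article that is not an error. The fault lies in the first step, which does state its method and its interpretation.
- **Reading the impact result.** A reader might infer that a null effect would be misattributed to the kit. The primary analysis is among survey participants, so coverage among those surveyed is the right figure for telling weak delivery from a weak kit.
- **Mitigation.** Services start from a random client list, peers seek people outside treatment, and the baseline survey precedes the intervention period. Baseline membership therefore cannot depend on having received a kit. But the list is random only among service clients and can be abandoned after week eight, and the people outside treatment are found by the peers who also distribute kits.

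The objection that this is only loose wording does not stand in full. The text gives a method and says what its result means, and the two do not match the protocol's own definition of the population.

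**Conclusion.** The point holds as a mismatch between a measure and its label. The linked proportion is coverage among survey participants, and the plan presents it as a proportion of the population. Selection tends to push it above reach in the population of people who use crack.

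That the reported figure will be too high is a stronger conclusion that a reader might draw, and the document does not support it. The size depends on uptake, local contact rates and second-survey participation, none of which is given. Under the assumed inputs the selection gap runs from none to 10 points or more, and about 4 points at the one contact share tied to a document figure. Missed matches could offset some or all of it.

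This is a descriptive process measure. The primary and secondary outcome analyses are not affected. The change is still worth making because it alters what is reported for objective 3 and costs little.

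**What to change.** In the process evaluation's Analysis section:

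1. Define the linked measure as kit receipt among **all** baseline-survey participants at intervention sites, whether or not they took the second survey.
2. Report it by site, and separately for service-recruited and peer-recruited participants.
3. Call it *coverage among survey participants*, not a proportion of the population.
4. Use *population reach* only for unique kit recipients divided by an independent local estimate of people who use crack, where one is available, with its uncertainty stated.

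Items 1 to 3 change wording and tabulation only. The data and the linkage are already planned. Item 4 needs local estimates that fit each site's catchment. The article gives national figures only, so it can only be optional. The downside is that the reported figure may be lower, and some sites may have no population-reach figure at all.
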